**Figure 2 fig2:**
[figure not shown]
Schedule of enrollment, interventions, and assessments. “√” means things will be done. t0: Baseline assessment. t1: The first week of the intervention. t2: 1-week post-intervention assessment. t3: The second week of the intervention. t4: 2-week post-intervention assessment.

### Informed consent

2.10

Trained and experienced clinical professionals will be responsible for obtaining informed consent from potential participants. Throughout this process, the research team will ensure that each potential participant comprehensively understands the study’s purpose, methodologies, potential risks and benefits, as well as the possible effects of participation on their health and overall well-being. The clinical professional will provide a thorough explanation of the informed consent form’s content, ensuring that participants can ask pertinent questions and receive satisfactory responses. Additionally, participants will be explicitly informed of their right to withdraw from the study at any time without experiencing any negative repercussions. This approach aims to uphold the autonomy of participants and guarantee that they possess adequate information and understanding when making decisions regarding their participation.

### Additional consent provisions for collection and use of participant data and biological specimens

2.11

No biological specimens are collected for research purposes.

### Interventions

2.12

#### Trial group

2.12.1

All participants were thoroughly informed that the intensity of electrical stimulation administered during the trial might fall below the conventional threshold of human sensory perception and that some may not feel the electrical stimulation. 40-Hz ES will be given at the affected side LI11 (quchi) of the patient, with an intensity starting at 0 mA and adding 0.1 mA each time to avoid pain to the patient tolerance (When the patient develops pain, immediately stop continuing to increase the current and drop 0.1 mA).

#### Control group

2.12.2

All participants were thoroughly informed that the intensity of electrical stimulation administered during the trial might fall below the conventional threshold of human sensory perception and that some may not feel the electrical stimulation. Sham ES will be given at the affected side LI11 (quchi) of the patient, although the power indicator of the electroacupuncture apparatus used in the control group was illuminated, the device was carefully configured to ensure that no electrical current was actually delivered to the participants.

#### Intervention description

2.12.3

The acupuncture intervention is shown in Figure 3. Use disposable sterile acupuncture needles (0.30 × 25 mm, Hwato, Suzhou Medical Supplies Factory Co., Ltd., China) to puncture LI11 and a non-meridian and non-acupuncture point adjacent to LI11. The precise location of the LI11 is the midpoint of the line connecting the LU5 and the lateral epicondyle of the humerus. The location of the LU5 and the lateral epicondyle of the humerus can be directly localized by the body surface structures. Use the electroacupuncture stimulation treatment instrument (Hwato SDZ-III, Suzhou Medical Supplies Factory Co., Ltd., China) to output 40-Hz bidirectional rectangular pulse current. Before using the electroacupuncture stimulation treatment instrument, adjust the intensity adjustment knob to 0 (no output), adjust the frequency adjustment knob to 40-Hz, set the time to 20 min, and then connect the two pairs of output electrodes on the machine to two needles, with an intensity starting at 0 mA and adding 0.1 mA each time to avoid pain to the patient tolerance (When the patient develops pain, immediately stop continuing to increase the current and drop 0.1 mA). At the end of the intervention, adjust the intensity adjustment knob to 0 (no output), the power should be turned off, and the electrode clamp should be removed from the needle shank and the needle inserted into the tissue should be removed. The intervention will be performed 5 times a week.

**Figure 3 fig3:**
[figure not shown]
A schematic diagram of the acupuncture intervention. LU5 belongs to the Hand Taiyin Lung Meridian, which is located in the elbow area, on the transverse stripe of the elbow, in the concave radial margin of the biceps brachii tendon. LI11 belongs to the Hand Yangming Large Intestine Meridian and is located at the lateral end of the transverse elbow stripe, with the elbow flexed, at the midpoint of the line connecting the LU5 and the Lateral epicondyle of the humerus. Place a dry sterile cotton ball between the two needles to prevent short circuits caused by accidental contact between the cathode and anode.

#### Criteria for discontinuing interventions

2.12.4

If the patient develops other medical conditions during the intervention that interfere with the intervention, the intervention should be discontinued immediately and the circumstances documented. If the patient has participated in the assessment and intervention for more than 2 weeks, the patient’s data should still be recorded and counted; if the patient initiates discontinuation of the intervention during the intervention, the intervention should be discontinued immediately and the reason for discontinuation should be recorded in a timely manner.

Interventions will be halted if unanticipated problems (UPs) or serious adverse events (SAEs) arise that raise concerns about the intervention’s safety. Additionally, if new information emerges during the trial that warrants discontinuation, the trial will be stopped accordingly. Currently, numerous published studies have utilized 40-Hz sensory stimulation to evoke gamma oscillations in healthy subjects and Alzheimer’s patients, and no serious adverse effects have been reported. Our group is conducting a clinical trial of 40-Hz sensory stimulation induced gamma oscillations for stroke rehabilitation, and no adverse events have occurred.

#### Strategies to improve adherence to interventions

2.12.5

Before the implementation of ES of patients, patiently explain the specific operation of acupuncture to patients in detail, so that patients can understand the safety of this intervention, so as to win the trust and cooperation of patients.

#### Relevant concomitant care permitted or prohibited during the trial

2.12.6

During the trial period, registered participants are prohibited from enrolling in other clinical trials. The research team will provide periodic reminders to participants to refrain from initiating any additional rehabilitation programs throughout the study duration. This approach is essential to maintain the validity and reliability of the research findings.

#### Provisions for post-trial care

2.12.7

Should participants incur any harm as a consequence of the trial, they will be provided with treatment in accordance with established medical protocols.

### Outcomes

2.13

All patients will receive baseline assessment, 1-week post-intervention assessment and 2-week post-intervention assessment. The primary outcome is the FMA-UE. The secondary indicators include EEG, NIHSS, MMSE and MBI.

#### FMA-UE

2.13.1

FMA-UE is primarily used to evaluate reflex activity, motor control, and muscle strength in the hemiplegic upper extremity, and it is widely used as a rehabilitation test and to record outcomes of recovery after stroke. It can make accurate quantitative assessment of the limb function of hemiplegia stroke patients, and the assessment is more comprehensive, which can intuitively and quickly reflect the abnormal movement patterns of patients (42). The FMA-UE includes a total of 33 upper limb proximal and distal limb movement-related items, with a total score of 66. The scoring criteria are as follows: each item is scored on a scale of 0, 1, and 2, with 0 being unable to complete at all, 1 being able to complete only part of the activity, and 2 being able to complete the prescribed movements, with higher scores and better motor function. Prior to each assessment, participants will be allowed to practice using their unaffected side to avoid learning effects. Studies have proved that the clinically important difference of the FMA-UE scores ranged from 4.25 to 7.25 points, and the improvement of FMA-UE score of 5.25 marks a significant improvement in upper limb motor function (40). We defined a clinically meaningful response as a 5.25-point in FMA-UE score based on previous research (43).

#### EEG

2.13.2

The EEG data will be collected through a 32-lead wireless EEG acquisition system (iRecorder, Shanghai Niantong Intelligent Technology Co., Ltd., China). A tranquil and electrically shielded examination room will be employed for the study. Participants will be instructed to remain awake and quiet while seated comfortably, refraining from engaging in any cognitive or mental tasks. All assessments will be conducted by a single EEG examiner. The system will possess a common-mode rejection ratio of 130 dB, an input impedance of 200 GΩ, and an input noise level of less than 0.2 μVrms, with a resolution of 24 bits. The sampling frequency will be established at 1000 Hz, and the impedance for each channel will be maintained below 20 kΩ. The data processing and analysis software Matlab2024a of THE MATH WORKS company and EEGLAB toolbox will be used to analyze EEG data offline (44). The reference electrode will be converted from the recorded Cz electrode to the average of all electrodes (45). Independent component analysis will be performed, and artifacts will be removed using the ADJUST algorithm (46). We perform spectral analysis on EEG data collected during resting state using the Hamming window and Fast Fourier Transform (FFT). Through FFT transformation, we analyze the absolute power of each frequency band, thereby elucidating the characteristics of EEG activity across different frequency ranges. The resting state electroencephalogram data are further analyzed using functional connectivity (FC) techniques. We employ filtering methods to remove power frequency interference and electromyographic noise, followed by the application of bandpass filters to extract gamma band signals. After filtering, we utilize the Hilbert transform to process the filtered signal from each electrode, which enables us to extract phase information. Subsequently, we calculate coherence as a measure of signal similarity between electrodes within the gamma band. Based on these calculations, we construct a connection matrix to visualize the connection strength and patterns among different electrodes using a network diagram. This comprehensive analytical approach reveals the characteristics and activity patterns of brain networks under the influence of 40-Hz ES. We will explore the relationship between changes in EEG parameters and other clinical outcomes to gain a more comprehensive understanding of the neurophysiological mechanisms underlying the effects of ES.

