Gamma oscillations (30–100 Hz), a synchronous neural activity common in many brain regions, are thought to be a functional feature of brain networks (15–18). This functional characteristic of the brain will change after stroke (19). Gamma oscillations have been demonstrated to promote neuroplasticity and neuroprotection by regulating synaptic connections and reducing neuronal damage with inflammatory responses in microglia (1, 20). Studies have proved that gamma oscillations enhance synaptic strength and modify neural network connections, promoting neuroplasticity and facilitating the reorganization and repair of damaged neural pathways in the brain, which underpins the recovery of upper limb motor function (21). Additionally, a recent research has demonstrated a significant positive correlation between increased gamma power and the FMA-UE scores of moderate to severe stroke patients during the recovery period (22). Inducing gamma oscillations has shown significant potential in promoting upper limb motor function recovery post-stroke, offering novel strategies and approaches for neurorehabilitation.

Previous trials have proved that a specific frequency of sensory stimulation as a neuromodulation technique, can provide a more comprehensive stimulation, activate sensory receptors induce brain gamma oscillation, activate the damaged nervous system, promote nerve recovery, by increasing the cerebral cortex excitability and arousal, improve the ischemic blood supply stimulation nerve function reconstruction (23–25). Sensory stimulation therapy has a low risk and fewer side effects, and currently there are only reports of using 40-Hz sensory stimulation to stimulate gamma oscillations to promote the recovery of cognitive function in Alzheimer’s disease mouse model or patients (26–29). There is a lack of research on the clinical efficacy and mechanism of applying 40-Hz sensory stimulation to induce gamma oscillations and promote the rehabilitation of upper limb motor function in stroke patients.

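### Gamma connectivity is measured only by plain scalp coherence, so a change in source power or residual muscle signal can pass as brain-network change

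*Protocol article*

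**What the plan says.** Section 2.13.2 (EEG) describes a resting 32-lead recording and a fixed processing chain.

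- Recording conditions: "A tranquil and electrically shielded examination room will be employed for the study", and "Participants will be instructed to remain awake and quiet while seated comfortably, refraining from engaging in any cognitive or mental tasks".
- Reference: "The reference electrode will be converted from the recorded Cz electrode to the average of all electrodes".
- Artefact removal: "Independent component analysis will be performed, and artifacts will be removed using the ADJUST algorithm". The text does not say that this step targets muscle.
- Connectivity pre-processing: "We employ filtering methods to remove power frequency interference and electromyographic noise, followed by the application of bandpass filters to extract gamma band signals".
- Phase: "we utilize the Hilbert transform to process the filtered signal from each electrode, which enables us to extract phase information".
- Connectivity measure: "Subsequently, we calculate coherence as a measure of signal similarity between electrodes within the gamma band".

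The electrode-by-electrode matrix is then read as showing how brain networks behave under 40-Hz stimulation. No other connectivity measure is named. The EEG section gives no band limits; the Introduction describes the band in general terms: "Gamma oscillations (30–100 Hz), a synchronous neural activity common in many brain regions".

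Section 2.15.1 plans Pearson correlations of change in FMA-UE with change in gamma-band power and in functional connectivity. Section 2.13 lists EEG among the secondary indicators, and section 2.1 calls the trial exploratory.

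**The concern.** Coherence between two scalp electrodes does not require two interacting brain regions. One source spread through the head by volume conduction produces it, and so does one muscle picked up at both sites. Both reach the electrodes with essentially no delay, and coherence gives zero-lag similarity full weight.

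The plan assigns muscle noise in the connectivity step to filtering. A filter separates signals by frequency, so muscle activity that shares the gamma band passes with the gamma signal. The Hilbert step extracts phase, from which a lag-sensitive measure could be built, but the measure named is coherence.

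The overall objective in the Introduction includes mechanism at the level of neural circuit and brain network, and this is the only network measure described. The Introduction also cites a positive correlation between gamma power and FMA-UE scores. If coherence moves with power, the two key EEG parameters in section 2.15.1 are not separate evidence: a power change could be reported a second time as a network change.

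**Working it through.** The protocol states no figure for this point, so there is none to reproduce. The check asks how much coherence arises when true interaction is zero.

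**Inputs from the protocol:** the coherence measure, 1000 Hz sampling and the Hamming/FFT spectrum (2.13.2); 30–100 Hz (Introduction). **Assumed and shown as ranges:** mixing, source and muscle levels. The simulations used 120 s of signal. ICA/ADJUST was not simulated.

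**Definition.** Coherency is C = S12/√(S11·S22), where S12 is the cross-spectrum and S11, S22 are the power spectra. Coherence is |C| or |C|². If independent sources are mixed without delay, S12 is real. |C| can then be large while the imaginary part of C is zero in expectation.

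**1. Shared component.** Two electrodes each carry an independent unit-variance source plus a common zero-lag component of variance v, so |C| = v/(1+v).
- v = 0.25: 0.25/1.25 = 0.20
- v = 0.5: 0.5/1.5 = 0.33
- v = 1: 1/2 = 0.50

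**2. Volume conduction.** Two independent sources each leak a fraction w into the other's electrode, so |C|² = (2w/(1+w²))².

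| w | formula | simulated | mean absolute imaginary part, simulated |
|---|---|---|---|
| 0 | 0 | 0.005 | 0.037 |
| 0.1 | 0.039 | 0.050 | 0.043 |
| 0.2 | 0.148 | 0.149 | 0.036 |
| 0.3 | 0.303 | 0.305 | 0.027 |
| 0.5 | 0.640 | 0.646 | 0.021 |

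Coherence climbs with the leak. The imaginary part stays at its noise level.

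**3. Change in power alone.** One source of amplitude g reaches two electrodes with fixed weight 0.7, plus independent unit noise. Then S = (0.7g)² and |C|² = (S/(S+1))².
- g = 1.0: S = 0.49; (0.49/1.49)² = 0.11
- g = 1.5: S = 1.10; (1.10/2.10)² = 0.27

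The simulation gave 0.11 and 0.27, with imaginary parts of 0.043 and 0.034. Nothing about connectivity changed between the two rows, only the amplitude of one source.

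**4. Muscle inside the band.** For a muscle signal assumed flat over 20–200 Hz, a 30–100 Hz band-pass keeps (100−30)/(200−20) = 70/180 = 39% of its power. Adding it equally to two independent brain signals, at amplitude 0, 0.25, 0.5 and 1 before the band-pass and relative to brain gamma, gave simulated |C|² of 0.006, 0.005, 0.017 and 0.11. Small residual muscle is harmless. Muscle comparable in size to the gamma signal is not.

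**The case against.** The plan has real protections. Recording is seated and at rest, and ICA with ADJUST is listed before the connectivity filtering. Both should reduce muscle artefact, and step 4 shows that low residual levels add almost nothing. How much muscle or mixing remains after these steps is unknown, so the figures above illustrate a mechanism and do not estimate its size in this trial. That stands. However, none of these steps removes volume conduction, and in the connectivity step the text assigns muscle noise to filtering.

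Lag-based measures discard genuine zero-lag coupling, so neither type of measure is clean. That also stands, and it argues for adding one rather than replacing coherence.

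Three stronger readings are tempting but unsupported.

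- *Mains hum also corrupts the measure.* Section 2.13.2 plans a shielded room and power-frequency filtering. With an assumed 50 Hz sinusoid of peak amplitude twice the brain-signal SD, squared coherence was 0.47 without a notch and below 0.001 with one.
- *The average reference creates false coherence.* For 32 independent channels it adds about (1/31)² = 0.001.
- *The gamma band is wrongly set.* Section 2.13.2 gives no cut-offs, and the 30–100 Hz range is general background in the Introduction. Cut-offs may sit in a fuller document.

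**Conclusion.** The concern holds in a limited form. Plain inter-electrode coherence, as the only connectivity measure, cannot separate a network change from a change in source power or in residual in-band muscle. The exposed analysis is the set of change-on-change correlations with FMA-UE in section 2.15.1, which randomisation does not protect.

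A reader might infer that the comparison between arms is biased. The documents do not support that. Static volume conduction, or equal muscle noise in both arms, raises coherence in both and creates no difference by itself. Source power or muscle activity would have to change differently by arm, and nothing in the documents shows that it does. If stimulation did raise gamma power, as the trial hypothesises, an arm difference in coherence would carry the same ambiguity.

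Nor does the point reach the primary FMA-UE comparison. EEG is a secondary indicator in an exploratory trial, so this is an inexpensive improvement to the mechanistic part. The conclusion assumes only that some zero-lag mixing remains after artefact removal; the sizes depend on the assumed mixing levels.

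**What to change.** In section 2.13.2:

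- Add a zero-lag-insensitive measure (weighted phase-lag index or imaginary part of coherency), computed from the Hilbert-transformed gamma signals already planned. Choose one before the data are analysed.
- Report it beside coherence, and carry both into the section 2.15.1 correlations.
- Claim a network-level effect only where the added measure agrees with coherence. If coherence alone moves, describe the result as a change in scalp coherence that may reflect power or muscle.
- State that muscle activity is handled by rejecting muscle components at the planned ICA step, rather than by filtering.

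The cost is a little more analysis on the same recordings and software. The drawback is that lag-based measures miss true zero-lag coupling, so a real network effect of that kind would go unclaimed. Coherence stays in the report for that reason.

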#### NIHSS

2.13.3

The NIHSS is now considered the primary tool for evaluating neurological changes in patients with acute ischemic stroke and for determining treatment options and predicting patient outcomes (47–49). The NIHSS Neurological Check consists of a comprehensive assessment comprising 11 items. These items assessment various neurological functions, including the level of consciousness—assessed through three components (level of consciousness, responses to questions, and execution of commands)—as well as best gaze, visual function, facial palsy, motor function of the arms and legs, limb ataxia, sensory perception, best language capability, dysarthria, and the presence of extinction or inattention. It shows good correlation with the volume of cerebral infarction measured by brain computed tomography (scan) at 7 days and also shows good predictive correlation of 3-month outcome (50, 51). The NIHSS possesses good interrater reliability (mean kappa = 0.69) and test–retest reliability when performed by neurologists and nonneurologists (mean kappa = 0.66–0.77) (52). Correlation analysis of FMA-UE scores with NIHSS scores will help us to determine whether improvement in neurological deficits correlates with recovery of upper limb motor function.

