### Inclusion/exclusion criteria

2.6

The inclusion criteria for the participants are the following:

Meet the criteria for ischemic stroke in the Chinese Guidelines for the Diagnosis and Treatment of Acute Ischemic Stroke 2023, and confirmed by CT or MRI of the head.The patient had a first-time stroke with unilateral hemiplegia.Onset ranged from 2 weeks to 3 months, and vital signs were stable.Age 45–80 years old.The patient had upper limb motor dysfunction in clinical manifestations, and FMA-UE scores in the 0–30 range.The patient can sit independently for 1 h or more.Patients who are in stable condition, conscious, have no aphasia or disorder, can understand the content of the scale, and cooperate with examination and treatment.The patient has not taken any sedative medication or muscle relaxant for 2 weeks.Informed consent to this trial, and signed written informed consent.

The exclusion criteria for the participants are the following:

Patients who are critically ill or in the acute phase and whose condition has not yet stabilized.Patients with deafness, aphasia, or severe cognitive impairment that make it difficult to communicate normally.Patients with systolic blood pressure > 180 mmHg or diastolic blood pressure > 110 mmHg, patients with severe cardiovascular, liver, kidney, blood, digestive, respiratory and other primary diseases, patients with mental illness, malignant tumors, venous thrombosis, osteoporosis, severe bleeding tendency and infection at the treatment site.Patients who are unable to recover with the study protocol or participate in other clinical experiments within 3 months or receive other related treatments in the middle of the study, which may affect the efficacy judgment of this study.Dystonia and previous motor dysfunction caused by other reasons.Pregnant and lactating women.Hemiplegia upper limb with previous trauma and bone and joint diseases.The patient is in a state of severe spasticity, i.e., modified Ashworth scale above grade IIII.The patient has pacemakers, cochlear implants and other instruments and equipment in the body.The patient has had vagus nerve surgery.The patient has sensory disturbances of the skin.

Data integrity is compromised and data will not be included in the analyses when the following:

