#### Statistical methods for primary and secondary outcomes

2.15.1

We will use SPSS 23.0 statistical software for statistical analysis. The measurement data with normal distribution and homogeneity of variance will be expressed as ($\bar{x}$ ± s). If the test of variance is homogeneous and all samples follow normal distribution, the *t*-test will be selected; if the variance is uneven or a sample does not follow normal distribution, a Chi-square test will be used. If the results of ANOVA or Chi-square test are significant, further multiple comparisons will be needed, such as the SNK method, LSD method, extended *t*-test. *p* < 0.05 will be considered as statistically significant.

We will conduct Pearson’s correlation analyses to precisely quantify the relationships between changes in FMA-UE scores and changes in key EEG parameters, specifically focusing on gamma - band power and functional connectivity. These analyses will allow us to determine the extent to which electroacupuncture - induced modulation of brain activity, as reflected in EEG measures, is associated with improvements in upper limb motor function. We will also explore the relationship between changes in EEG parameters and other clinical outcomes to gain a more comprehensive understanding of the neurophysiological mechanisms underlying the effects of electroacupuncture.

We will utilize mediation and moderation analyses to dissect the complex interplay between neurological impairment (NIHSS), cognitive function (MMSE), daily living activities (MBI), and the effects of electroacupuncture on motor recovery. Specifically, we will investigate:

Whether improvements in cognitive function (MMSE) or daily living activities (MBI) mediate the relationship between electroacupuncture and gains in motor function (FMA - UE), suggesting that electroacupuncture’s effects on motor function are partially mediated by cognitive or functional improvements.Whether pre - existing levels of neurological impairment (NIHSS), cognitive function (MMSE), or daily living activities (MBI) moderate the effect of electroacupuncture on motor recovery, influencing the magnitude of the treatment response.

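### The NIHSS score to be correlated with FMA-UE itself includes arm motor function, so a significant correlation cannot show that deficits beyond the arm recover with it

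*Protocol article*

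**What the plan says.** Section 2.13.3 of the protocol article describes the content of the NIHSS: "The NIHSS Neurological Check consists of a comprehensive assessment comprising 11 items". The functions it names include "motor function of the arms and legs, limb ataxia, sensory perception". No item is set aside and no subscore is named, so the natural reading of NIHSS scores is the total.

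The section ends with the planned use: "Correlation analysis of FMA-UE scores with NIHSS scores will help us to determine whether improvement in neurological deficits correlates" with recovery of the arm.

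Section 2.13.1 describes the other variable: "FMA-UE is primarily used to evaluate reflex activity, motor control, and muscle strength in the hemiplegic upper extremity". It adds: "The FMA-UE includes a total of 33 upper limb proximal and distal limb movement-related items, with a total score of 66". Section 2.6 admits only patients with "FMA-UE scores in the 0–30 range".

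The article nowhere mentions that the two scales share content.

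**The concern.** One variable measures arm motor function. The other is a sum that contains arm motor function. If the arm improves, FMA-UE rises and the arm part of the NIHSS improves with it, whatever happens to gaze, face, leg, speech or any other NIHSS function. The two instruments score the arm differently, so the overlap is of construct and not of identical items, but it still pushes the correlation away from zero.

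What is at stake is the sentence that will be written from the result. A significant correlation reported as showing that neurological improvement accompanies arm recovery will be read as a statement about the nervous system more broadly. The planned analysis cannot separate that from the arm being measured twice. The trial's stated aim includes mechanism as well as efficacy, so such a sentence is likely to be given weight.

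**Working it through.** The article states no expected NIHSS correlation, so there is no figure of its own to reproduce. The check asks how large a correlation the overlap alone could produce.

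**Inputs from the article**
- 50 patients in total, 25 per group (Sections 2.1 and 2.2).
- Drop-out of around 20% (Section 2.2): 50 × 0.8 = 40 completers. This agrees with the stated 20 per group before inflation, 20 / 0.8 = 25.
- Significance at p < 0.05 (Section 2.15.1), two-sided as in Section 2.2.

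**Inputs assumed, because the article does not give them**
- s, the share of NIHSS variance carried by the arm item: 0.10 to 0.50.
- ρ, the absolute correlation of the arm item with FMA-UE: 0.5 to 0.8.
- All other NIHSS items are unrelated to FMA-UE and to the arm item, so there is no wider neurological link.
- A Pearson correlation over both groups together. Section 2.15.1 names Pearson for the EEG correlations and does not name a coefficient for this one.

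**Formula.** Write NIHSS = arm + rest. With the rest unrelated, the covariance of NIHSS with FMA-UE is the covariance of the arm item with FMA-UE. Dividing by the standard deviations gives

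|r(total)| = ρ × √s

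**Ends of the range**
- Mildest: 0.5 × √0.10 = 0.16
- Strongest: 0.8 × √0.50 = 0.57

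**Cut-off.** The smallest |r| with p < 0.05 is t / √(n − 2 + t²), where t is the 97.5% point on n − 2 degrees of freedom. This is 0.312 at n = 40 and 0.279 at n = 50.

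**Chance of a significant result** (simulation, 40,000 runs per case):

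| s | ρ | \|r(total)\| | n = 40 | n = 50 |
|---|---|---|---|---|
| 0.10 | 0.5 | 0.16 | 16% | 19% |
| 0.20 | 0.6 | 0.27 | 39% | 48% |
| 0.20 | 0.7 | 0.31 | 51% | 61% |
| 0.30 | 0.7 | 0.38 | 70% | 80% |
| 0.50 | 0.8 | 0.57 | 98% | 99% |

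**After the fix.** With the arm item removed and still no wider link, the expected correlation is 0. The simulated chance of p < 0.05 is 5.1% at both sample sizes, which is the nominal level.

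**The case against.** The strongest reply is that the article asks whether neurological improvement goes with arm recovery, not whether deficits other than the arm do. Arm paresis is a neurological deficit and the NIHSS total is the chosen measure of such deficits, so for the question as worded the total is a legitimate variable. This stands: the full-total correlation is open to misreading, not invalid. It also means that the question as worded is partly answered by the make-up of the scale, which is why a second figure is needed.

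Two further replies also stand in part. First, s and ρ are assumptions, and a range of 16–99% does not show how much the overlap matters in this trial. It is tempting to argue that, since every patient has a badly affected arm, the arm item must dominate the total. That does not follow, because a deficit shared by all patients need not vary much between them or change much in two weeks. Section 2.6 also limits aphasia, impaired consciousness and skin sensory disturbance, which pushes the other way. The net share is unknown. Second, the trial is described as exploratory and this is one secondary correlation.

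A reader might also infer that the overlap spoils the planned "mediation and moderation analyses to dissect the complex interplay between neurological impairment (NIHSS") and related measures in Section 2.15.1. The document does not support that. NIHSS enters there as a pre-existing, baseline moderator; the mediators listed are MMSE and MBI. Shared content makes baseline NIHSS prognostic for FMA-UE, but it does not create a treatment-by-NIHSS interaction. Simulated with s of 0.2 or 0.5, ρ of 0.6 or 0.8, a treatment effect and no true interaction (20,000 runs each), the interaction test rejected in 4.9–5.1% of runs at n = 40 and n = 50.

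**Conclusion.** The point holds for the correlation in Section 2.13.3 only, and it is minor. That the overlap exists, and which way it pushes, follow from the article's own descriptions of the two scales. Its size does not: the correlation of 0.16–0.57 and the 16–99% chance of significance rest on assumed values of s and ρ and on the other items being unrelated. Every case examined lies above the nominal 5%.

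The consequence is a limit on interpretation. A significant correlation with the full total is compatible with no deficit beyond the arm having moved with FMA-UE. It would be going too far to call the total an improper measure or to carry the point over to the moderation analysis. The FMA-UE comparison between groups and the sample size are untouched.

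**What to change.** In Section 2.13.3, state that the change in FMA-UE will be correlated with the change in NIHSS minus the affected-arm motor item, and that the correlation with the full NIHSS total will be reported beside it. Any statement about neurological recovery beyond the arm should rest on the reduced score. The full-total figure can be described as including arm function.

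The cost is one derived variable, with no extra visit, patient or assessment. There is one condition: the NIHSS is scored item by item, but the article does not say that item scores are entered in the database. They need to be kept there, or at least the affected-arm item alongside the total.
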